## Abstract

**Background:**

Home treatment (HT) is a treatment modality for patients with severe mental illness (SMI) in acute mental crises. It is frequently considered equivalent to psychiatric inpatient treatment in terms of treatment outcome. Peer Support (PS) means that people with lived experience of a mental illness are trained to support others on their way towards recovery. While PS is growing in international importance and despite a growing number of studies supporting its benefits, it is still not comprehensively implemented into routine care. The HoPe (Home Treatment with Peer Support) study investigates a combination of both – HT and PS – to provide further evidence for a recovery-oriented treatment of psychiatric patients.

**Methods:**

In our randomized controlled trial (RCT), HT with PS is compared with HT without PS within a network of eight psychiatric clinical centers from the North, South and East of Germany. We investigate the effects of a combination of both approaches with respect to the prevention of relapse/recurrence defined as first hospitalization after randomization (primary outcome), disease severity, general functioning, self-efficacy, psychosocial health, stigma resistance, recovery support, and service satisfaction (secondary outcomes). A sample of 286 patients will be assessed at baseline after admission to HT care (data point t_0_) and randomized into the intervention (HT + PS) and control arm (HT). Follow-Up assessments will be conducted 2, 6 and 12 months after admission (resulting in three further data points, t_1_ to t_3_) and will be analyzed via intention-to-treat approach.

**Discussion:**

This study may determine the positive effects of PS added to HT, prove additional evidence for the efficacy of PS and thereby facilitate its further implementation into psychiatric settings. The aim is to improve quality of mental health care and patients’ recovery as well as to reduce the risk of relapses and hospitalizations for patients with SMI.

**Trial registration:**

The trial is registered with ClinicalTrials.gov: NCT04336527, April 7, 2020.

## Background

There are two innovative approaches in mental health care with a growing importance for especially treatment of patients with severe mental illness (SMI): Home Treatment (HT) – acute psychiatric care at home – and Peer Support (PS) – accompanying patients by individuals with lived experience in mental health crisis.

HT is a care model providing an alternative to acute inpatient stays in clinical settings as mobile teams visit patients in their home setting, internationally also referred to as crisis resolution teams (CRT) [1, 2]. Patients with SMI make up the main population receiving HT interventions [3]. In Germany, in addition to regional pilot projects [4], HT was recently implemented into regular psychiatric care as Inpatient Equivalent Home Treatment (IEHT) by law (PsychVVG, technical term coined by the Federal Ministry of Health: *Stationsäquivalente Behandlung, STÄB* – agreed on Jan 1, 2017, entered into force as of Jan 1, 2018; [5]). The operationalized HT model varies and surveys have revealed divergence in organization and implementation [6, 7], resources for home treatment (HT), and models of service delivery [8]. There have been some inconsistent findings regarding the efficacy of HT and the magnitude of changes in outcome, e.g. in reducing admission and days in admission [9–11]. Furthermore, the number of randomized controlled trials (RCT) investigating HT is limited. Nonetheless, a growing number of studies supports its positive effects: The 2009 National Institute for Health and Care Excellence (NICE) pooled reanalysis of clinical guidelines for Schizophrenia [12], which included 883 participants and six RCTs, found strong evidence for the reduction of admissions, shorter treatment duration, and fewer incidents of dropout while being treated, as well as increased satisfaction and cost-effectiveness, compared with standard care (admission to psychiatric wards). The latest Cochrane review of crisis intervention for patients with SMI also included two RCTs (mobile crisis teams, crisis units based in home-like residential houses). It showed a reduction of family burden and improvements of mental and global state, compared to standard care [13]*.* Given specific HT characteristics and the importance of model fidelity, a systematic review including 16 studies of different methodologies (RCTs as well as natural experimental studies) also indicates that HT can reduce hospital admission and inpatient bed days and increase patients’ satisfaction, compared to standard care [14]. These positive results are in line with other German studies either showing HT comparably effective as inpatient treatment [15, 16] or favoring HT against inpatient treatment concerning risk of hospital readmission and length of stay [17], depressive symptom severity, clinical and functional impairment and cost-effectiveness [18], service disengagement, psychopathology, psychosocial functioning, quality of life, satisfaction with care, adherence, and involuntary admissions [19]. A recent cluster-randomized trial proved even lower inpatient admissions and bed-use as well as an increase of staff psychological health after a one-year improvement program for crisis resolution teams [20, 21].

In a naturalistic study conducted in 17 German care networks providing HT, an increase of patients’ psychosocial functioning was related to staff experience and staff’s effort invested [22]. In a systematic review with 13 papers regarding service users’ experiences with HT besides ‘access and availability’ and ‘dealing with crisis in an everyday life contact’ the fact of ‘being understood as “normal” human beings’ was identified as key point of HT interventions [23]. These might be factors specific to PS.

PS workers use their personal background in mental health crises to support patients. In Germany, they can complete e.g. an Experienced Involvement (EX-IN) training of PS education [24] and contribute to mental health care by sharing their experiences and setting an example for recovery. Internationally various forms of PS are implemented in different countries [25].

Reviews on PS report few RCTs [26–28] in a wide range of different PS service settings. Results show that PS encourages hope, empowerment and recovery [27], and quality of life in patients with SMI [26]. Furthermore, there was a small difference in crisis and emergency service use as well as in meeting clients’ needs favoring the involvement of peers [28]. Further reviews also including non-randomized and some more recent controlled trials [29, 30] show significant differences in patient activation, hope, empowerment, and self-efficacy. Single RCTs show that peer-led groups positively affect internalized stigma [31], illness-management and adherence [32], and users’ social networks and support [33]. Whereas some reviews did not find remarkable differences in clinical outcomes like mental health symptoms or service use and hospitalization [27, 28], a recent RCT showed a reduced rate of hospital readmissions in a group that received peer supported interventions compared to a control condition [34]. Because the number of studies is limited and quality of evidence is partially low [35], high quality RCTs with clearly defined interventions, sufficient peer training, large sample sizes, adequate randomization, blinding of measurements, and the use of recovery outcomes with longer follow-up periods are called for [27, 28, 36]. Furthermore, an important aspect is to evaluate the fidelity of PS interventions and the principles underlying the role of PS and the positive effects of PS work [37].

### Objectives

Although both treatment options – HT and PS – are explicitly recommended in the German guidelines on psychosocial therapies regarding SMI [38], they are still considered innovative, are not comprehensively implemented across Germany [39] and are seldom combined. Following the successful implementation of peer projects in Germany, e.g. at the University Medical Centre Hamburg-Eppendorf [40], the effects of PS added to HT deserve evaluation, given PS might strengthen HT. The aim of the present study is to investigate the efficacy of the combination of both approaches in acute care – a HT plus PS intervention versus HT alone – to improve mental health care for patients with SMI.

### Hypotheses

It is hypothesized that a peer-supported home-delivered treatment (HT plus PS) is more efficacious than a professional-led home-delivered treatment (HT alone) with respect to the time until (first) hospital readmission (primary outcome), self-efficacy, psychosocial health, recovery orientation, stigma-resistance, and service satisfaction. Furthermore, it is hypothesized, that a peer-supported home delivered treatment (HT plus PS) is as effective as a professional-led home-delivered treatment (HT alone) with respect to disease severity and general functioning.

### Design

The trial is designed as a prospective open multicenter parallel group RCT to test the efficacy of HT with PS (intervention group) against sole HT (control group) at eight different study sites throughout Germany. Patients admitted to HT care are randomly allocated to the intervention and control group in a 1:1 ratio (block randomization stratified by study site). All participants will provide written informed consent before inclusion in the study.

## Methods

### Study setting

Data collection takes place at eight psychiatric hospitals, both academic and community clinics, in both rural and urban environments in the North, East, and South of Germany. All settings offer HT as regular care for psychiatric patients. In most cases, PS workers are already part of the HT teams and there has been a longstanding cooperation between HT teams and external PS workers. In some cases (additional) PS workers were employed within the HT team during study preparation. All study sites are experienced in working with PS workers. The location of all study sites can be obtained from the affiliations.

Data collection starts individually at the participating hospitals due to individual organizational prerequisites as well as delays caused by the current COVID-19 pandemic. Each study site will recruit patients for 12 months which are followed for at least 12 months (with the last individual measurement point t_3_ for secondary outcomes 12 months after t_0_, i.e. admission). For the primary outcome all patients are followed until one year after the last patient was included in the study at a study site. An extension of the recruitment period for each study site for up to 6 months for delays in patient acquisition due to COVID-19 restrictions and concerns (hospital closures, reluctant patients, etc.) was granted to ensure sufficiently large sample sizes. The first participating hospital started recruitment in July 2020, the last hospital is expected to start data collection at the latest in October 2021.

### Eligibility criteria

Care providers administering the intervention include subjects with a minimum age of 18 years, a diagnosis of an SMI (defined by diagnoses of ICD-10: F2, F3, F6, F41, F42), sufficient German language skills, and the indication of hospital admission because of an acute mental health condition. Exclusion criteria are a primary diagnosis of organic or substance use disorders (ICD-10: F0 or F1 [41]), acute suicidality, and a verbal or cognitive impairment severe enough to be unable to give written informed consent.

### Interventions

Patients in the *intervention group* receive a combination of HT by a multi-professional team with PS: PS workers are involved during the whole treatment duration. After discharge a maximum of five additional contacts are possible. Contacts to a PS worker take place at least one time per week in 1:1 contacts or in combination with other members of the HT team. Important aspects of PS contacts are defined as focus on personal resources, support of self-determination and autonomy, practical support in daily tasks, recover- and need-orientation, building bridges between patients and care providers, and trialogical work with inclusion of relatives or close persons. The so-called ‘trialogue’ format [42] is a term used in Germany to designate discussion meetings involving peers, carers and professionals focusing on the experience of, coping with, and recovery from mental health problems with special attention to the peer, carer and professional perspectives, contrasts, differences and perhaps similarities in experience. As far as possible (e.g. due to limited working hours), PS workers are included into all relevant treatment decisions. To ensure a standardization of treatment, an intervention guideline was established together with PS workers. Furthermore, there was an online training for PS workers regarding relevant aspects of peer work and the peer role within the intervention. All eligible PS workers had to have completed a standardized PS training, e.g. *Ex-In (Experienced Involvement)* [24] or *Honest, Open, Proud* [31, 43].

The *control group* receives conventional HT by a multi-professional team without contacts to a PS worker (treatment as usual). Multi-professional teams consist of nursing staff, psychiatrists/physicians, occupational therapists, social workers, and psychologists/psychotherapists. They provide acute mental health treatment by mobile care teams within the patients’ home setting or familiar environment that is equivalent to inpatient treatment (i.e. crisis intervention, supportive and therapeutic conversations, pharmacotherapy, support in daily life and problem solving, transfer to outpatient care and support [1, 44].

The duration of treatment depends on the individual clinical indication and may vary between two and several weeks, equivalent to inpatient stays. In case of readmission within the first six months after study enrolment patients receive the same intervention as during their first treatment – after this period of time they receive treatment as usual. Patients within the control group do not receive any PS by caregivers during the whole study period.

Fidelity of treatment is measured by use of a fidelity scale examining adherence to the intervention protocol in line with Lloyd-Evans and colleagues. [45].

### Outcomes

Primary outcome is *time to first readmission to inpatient hospital treatment* (follow-up monitoring until one year after the last patient was included).

#### Secondary outcomes are:

Change from baseline in *self-efficacy expectation* mean scores as assessed by the German scale “Skala zur Allgemeinen Selbstwirksamkeitserwartung” [SWE] [46].Change from baseline in *psychosocial health* mean scores as assessed by the German scale “Hamburger Module zur Erfassung allgemeiner Aspekte psychosozialer Gesundheit für die therapeutische Praxis” [Health-49] (subscales: somatoform complaints, depressiveness, phobic anxiety, psychological well-being, interactional problems, self-efficacy, activity and participation, social support, social stress [47]).Change from baseline in *stigma resistance* mean scores as assessed by the “Internalized Stigma of Mental Illness” [ISMI] scale – subscale stigma resistance [48].Change from baseline in *disease severity* mean scores as assessed by the “Clinical Global Impression” [CGI] scale [49].Change from baseline in *general functioning* mean scores as assessed by the “Global Assessment of Functioning scale [GAF] [50].Change from baseline in recover support as assessed by [INSPIRE] [51].

Times of assessment are at admission, and two, six, and twelve months after admission.

#### Further secondary outcomes are:

Means in *service satisfaction* scores as assessed by the German version of the Client Satisfaction Questionnaire [ZUF-8] [52].Means in *recovery support* scores as assessed by Brief INSPIRE [51].

Both are assessed at two and six months after inclusion into study.

### Participant timeline

The participant timeline is visualized in Fig. 1.

**Fig. 1 Fig1:**
[figure not shown]
Participant Timeline

### Sample size

For the purpose of sample size calculation, data for the HT alone group were collected from routine data of University Medical Center of Hamburg-Eppendorf, Department of Psychiatry and Psychotherapy. For the HT plus PS group data was collected from a former in-house study (unpublished routine data). From these data, one-year admission-free survival rates of 58% and 73%, respectively, were calculated corresponding to a hazard ratio of 0.577. To detect a difference between random groups of this order of magnitude with a power of 80%, *N* = 254 patients in total (127 patients per group; total event count = 106) are required if the recruitment takes 12 months and there are at least 12 months follow-up to an administrative censoring. This calculation includes a 30% loss-to-follow up over two years of follow-up time. With an accrual period of 18 months and the same assumption as above a sample size of *N* = 232 (total event count 106) is needed. This latter analysis was only added since recruitment intensity might be low due to COVID-19 restrictions. Additionally, it was checked how many patients would be needed to demonstrate a medium effect size (Cohen’s d = 0.4) with a power of 80% and a two-sided type I error of 5% in the secondary continuous outcomes. This resulted in 100 patients per group (200 patients in total) and with an expected dropout rate of 30%, in 286 patients in total (143 patients per group). Therefore, the total sample size of 286 was chosen. Sample size was calculated with PASS 2008 based on the logrank test (using proportion surviving) [53] and the two-sample t-test using an effect size.

### Recruitment

Patients regularly admitted to HT at one of the eight participating study sites and fulfilling eligibility criteria are informed about the study by care providers at time of admission. In most cases, patients are directly admitted. Nonetheless, it is also possible that they are transferred from inpatient treatment to HT. Patients receive verbal and written information about the study. If study information is not possible due to acute symptom severity, admission to the study can be delayed for up to 14 days until informed consent can be given. Until enrolment to the study, these patients receive standard HT care without involvement of peers. For enrolment, a minimal planned duration of treatment of two (further) weeks or ten home visits is predefined. Before giving written informed consent, patients have the possibility to additionally consult local research teams for patient information. This offer holds for the duration of the entire study. After having given written informed consent, care givers contact the local research team, who is then conducting the first telephone interview (see below). Study participation is voluntary. If negated or in case of dropout, patients receive treatment as usual by the HT team without any harm. The recruitment period continues for up to 18 months at each site to reach an average target sample of 36 participants per site.

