#### Blinding

HT care providers and patients are blinded at time of baseline ratings (GAF; CGI). Randomization and allocation to treatment are done after baseline rating. For compelling reasons, HT care providers’ second rating of GAF and CGI at time of discharge is not blinded nor are patients at further times of data acquisition because they will have received intervention. Research associates accomplishing telephone interviews are blinded whenever possible. That is, at all four measurement points, namely at admission (t_0_), 2 months after admission (t_1_), 6 months after admission (t_2_), and 12 months after admission (t_3_). In telephone interviews at t_1_, t_2_, and t_3_ patients are explicitly instructed not to reveal any information about their group allocation against research associates to ensure blinding of outcome assessment. The statistical analysis will be conducted in a blinded manner.

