### Methods: data collection, management, analysis

#### Data collection methods

Data are collected at baseline by HT staff and research associates, at time of discharge by HT staff, and at the three follow-ups (at 2, 6 and 12 months) by local research teams.

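### Patients may contact the local research team throughout the study, but the non-disclosure instruction that protects that team's blinding is stated only for the follow-up interviews

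*Protocol article*

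**What the plan says.** The Recruitment section of the protocol article sets the contact rule. Ahead of consent, "patients have the possibility to additionally consult local research teams for patient information", and "This offer holds for the duration of the entire study".

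The same section gives the baseline interview to that team: after consent, "care givers contact the local research team, who is then conducting the first telephone interview". The section on data collection methods assigns the later data to it as well, "at the three follow-ups (at 2, 6 and 12 months) by local research teams".

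The Blinding section sets the blinding rule. "Research associates accomplishing telephone interviews are blinded whenever possible", and it goes on to name all four measurement points. It acknowledges that patients are not blinded after baseline. To protect the blinding of outcome assessment it relies on one measure: "In telephone interviews at t_1_, t_2_, and t_3_ patients are explicitly instructed not to reveal any information about their group allocation".

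**The concern.** One rule gives patients a standing invitation to talk to the local research team. Another asks the interviewers in that team not to know the arm. The measure that should reconcile the two covers the interviews and nothing else.

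A question asked between interviews can easily reveal the arm, because the arms differ in visible ways. Under Interventions, only one arm has weekly peer contacts and up to five further peer contacts after discharge, and the assigned treatment is repeated on readmission within six months of enrolment. A question on any of these would show the interviewer which arm the patient is in, if the interviewer is the one who answers.

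The outcomes at stake are self-ratings given aloud over the telephone, where an interviewer can prompt or clarify. All but one of the outcomes with a superiority hypothesis are of this kind: self-efficacy, psychosocial health, recovery orientation, stigma resistance and service satisfaction. The exception is the primary outcome. The secondary continuous outcomes also fixed the trial size: 286 patients, against 254 for the primary outcome. The Background itself lists blinded measurement among the features that peer-support trials need.

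**Working it through.** No figure in the plan depends on this point, so there is nothing to recompute. The check is to set the statements side by side.

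1. **Who is the contact?** The local research team (Recruitment).
2. **For how long?** The whole study (Recruitment). Patients learn their arm from the home-treatment staff at the visit after the first interview (Allocation). The offer therefore continues after the patient knows the arm.
3. **Who interviews?** The local research team, at baseline (Recruitment) and at 2, 6 and 12 months (Data collection methods). The contact and the interviewers carry the same label, and no section separates the people who answer questions from those who interview.
4. **What is the blinding aim?** Interviewers blinded as far as possible, at all four points (Blinding). The baseline interview is not exposed to this route, because the patient does not yet know the arm. The three follow-ups are.
5. **What guards it?** The instruction to patients, stated for the t1, t2 and t3 interviews (Blinding). No section extends it to other contacts with the team.

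Steps 2, 3 and 5 together leave a gap: contact after allocation, with the team that interviews, outside the interviews and without the instruction.

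**Which outcomes are exposed**

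| Outcome | Source | Exposed to this route? |
|---|---|---|
| Time to first readmission (primary, the only confirmatory analysis) | Hospital IT database | No |
| CGI, GAF | Home-treatment staff, openly unblinded at discharge | No |
| SWE, Health-49, ISMI, INSPIRE, ZUF-8 (exploratory) | Taken here as telephone self-ratings | Yes, at follow-up |

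The last row rests on a reading. The article says that most secondary data come from the telephone interviews but does not list the instruments used in them.

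**Outer limit of scope.** With no dropout there are 286 × 3 = 858 follow-up interviews. If the planned 30% dropout all occurred before the first follow-up, 286 × 0.70 ≈ 200 patients would remain, giving 200 × 3 = 600 interviews. ZUF-8 and Brief INSPIRE are taken only at 2 and 6 months, so at most 286 × 2 = 572 times each. These figures count interviews held. They do not estimate interviews unblinded, since only patients who contact the team and reveal the arm are exposed by this route, and the document gives no frequency for either.

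**The case against.** Several objections are fair.

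- **Role against team.** Blinding is asked of the associates who interview, while the contact offer names a team. A site may have one person answer questions and another interview. That division could stand in the full protocol or in the interview guideline, neither of which is shown. This stands: the article shows an open route, not a breach. A reader might infer that the person answering is the interviewer, but no section says so.
- **Strength of the blinding rule.** A reader might infer that interviewers are strictly required to stay blind. The text qualifies the aim with the words as far as possible, so there is no outright contradiction.
- **Likelihood of disclosure.** A reader might infer that patients who call will usually reveal their arm. The offer is for study information and is introduced for the time before consent. Questions about treatment may well go to the staff who visit the patient at home. The document does not support a statement about frequency.
- **Other safeguards.** A reader might infer that interviewer blinding is all that protects these outcomes. It is not: the section on collecting secondary outcomes also describes a prepared and trained guideline for the interviews and visual answer scales given out beforehand. Both limit interviewer influence. Since patients know their arm, interviewer blinding protects self-ratings only in part in any case.
- **Consequence.** No confirmatory conclusion is touched.

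These arguments reduce the weight of the point but do not close the gap. The other safeguards do not keep the arm from the interviewer. The article also goes beyond silence here: it states an open-ended contact rule and a narrower safeguard.

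**Conclusion.** The point holds as a limited one. The contact rule works against the stated blinding aim, because the instruction to patients does not cover contacts outside the follow-up interviews. It concerns the exploratory, interview-based secondary outcomes and leaves the primary outcome and the CGI and GAF ratings untouched.

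The size of any bias cannot be derived from the document. It would depend on how many patients contact the team, how many reveal the arm, whether the same person interviews them, and whether interviewer influence runs in favour of one arm. None of these is given, so attaching a standardised effect size would be guesswork.

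The conclusion assumes that the same label means the same group of people and that the instruments named above are taken in the telephone interviews. If the full protocol already separates the roles, the route is largely closed and only the wording of the article needs to change. It is a cheap improvement, worth making because it lowers a risk of bias at almost no cost.

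**What to change.** 1. **Recruitment.** Direct patients' questions after randomisation to an existing role that does not interview that patient. The offer before consent can stay as it is.
2. **Blinding.** Extend the instruction not to reveal the arm from the t1 to t3 interviews to every contact with the research team.
3. **Interview form and analysis.** Add one item at the end of each follow-up interview recording whether the arm became known to the interviewer. Report unblinding by arm, and repeat the secondary analyses without the affected interviews as a sensitivity analysis. Unblinding happens after randomisation and may be related to the arm, so this belongs beside the full analysis and does not replace it.

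The cost is a changed contact line in the patient information and one extra form item. Recruitment began in July 2020, so patients already enrolled would have to be told of the new contact. Treatment, the primary endpoint and the sample size do not change. Interviews can stay with the local teams, since local interviewing is not in itself a defect.
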